## Abstract

**Background:**

Obesity is a major public health problem in both developed and developing countries alike and leads to a series of changes in respiratory physiology. There is a strong correlation between obesity and cardiopulmonary sleep disorders. Weight loss among such patients leads to a reduction in these alterations in respiratory physiology, but clinical treatment is not effective for a long period of time. Thus, bariatric surgery is a viable option.

**Methods/Design:**

The present study involves patients with morbid obesity (BMI of 40 kg/m^2 ^or 35 kg/m^2 ^to 39.9 kg/m^2 ^with comorbidities), candidates for bariatric surgery, screened at the Santa Casa de Misericórdia Hospital in the city of Sao Paulo (Brazil). The inclusion criteria are grade III morbid obesity, an indication for bariatric surgery, agreement to participate in the study and a signed term of informed consent. The exclusion criteria are BMI above 55 kg/m^2^, clinically significant or unstable mental health concerns, an unrealistic postoperative target weight and/or unrealistic expectations of surgical treatment. Bariatric surgery candidates who meet the inclusion criteria will be referred to Santa Casa de Misericórdia Hospital and will be reviewed again 30, 90 and 360 days following surgery. Data collection will involve patient records, personal data collection, objective assessment of HR, BP, neck circumference, chest and abdomen, collection and analysis of clinical preoperative findings, polysomnography, pulmonary function test and a questionnaire on sleepiness.

**Discussion:**

This paper describes a randomised controlled trial of morbidly obese patients. Polysomnography, respiratory mechanics, chemosensitive response and quality of life will be assessed in patients undergoing or not undergoing bariatric surgery.

**Trial Registration:**

The protocol for this study is registered with the Brazilian Registry of Clinical Trials - ReBEC (RBR-9k9hhv).

## Background

Obesity is currently one of the most serious public health problems. The prevalence of this condition has grown in an accentuated fashion in recent decades, even in developing countries, leading to a global epidemic. Over 1.6 billion adults worldwide are overweight, among which 400 million are obese. The World Health Organisation predicts that 10% of the global population will be obese by 2015 [1]. As poverty has been undergoing a process of eradication, obesity has become a more frequent and more serious problem than malnutrition [2,3]. In adults, overweight is characterised by a body mass index (BMI) between 25 kg/m^2 ^and 29.9 kg/m^2 ^and obesity is defined beginning at 30 kg/m^2 ^[4].

When excess weight reaches very high values (BMI ≥ 40 kg/m^2^), obesity is considered a severe dysfunction due to the association with diseases that are either caused or aggravated by this condition, corresponding to grade III obesity, which is also denominated morbid obesity [4]. The most frequent comorbidities are systemic arterial hypertension [5,6], type II diabetes mellitus [7], obstructive sleep apnoea [8], degenerative joint disease [9], dyslipidemia, coronary disease [10,11], respiratory dysfunction [12] and psychosocial problems [13].

Obesity is the most important risk factor for obstructive sleep apnoea (OSA), especially with fat build-up in the upper portion of the abdomen and the neck region. At least 60 to 70% of patients with OSA are obese [14]. Moreover, the incidence among patients with Grade III obesity is 12-fold to 30-fold greater than that in the general population [15,16]. OSA is characterised by recurrent episodes of partial or complete obstruction of the upper airway during sleep in the presence of ventilatory effort, with a consequent drop in oxyhemoglobin saturation, generating negative intrathoracic pressure and arousals [17]. The gold standard for the diagnosis of OSA is basal nocturnal polysomnography (PSG), which is the simultaneous recording of physiological parameters during a night of sleep, involving the analysis of sleep stages, breathing pattern, cardiovascular function and body movements [18,19].

The association between obesity and respiratory sleep disorders was first described in 1918 by William Osler, who was reminded of a Charles Dickens' characters nicknamed "John, the fat boy", a plethoric snorer and terribly sleepy [20]. The treatment of obesity in these patients has since become a priority [21]. Common diseases such as obesity and hypertension should not be analysed without considering respiratory sleep disorder as a possible causal factor. In recent years, the prevalence of such disorders has grown, affecting 40% of the general population [22,23].

The aim of the treatment of obesity is to improve both health and quality of life through enough of a reduction in body weight to eliminate or improve comorbidities and promote psychological wellbeing [24]. Medical management of obesity is routinely the first line of treatment prescribed by physicians and lay persons alike. Medical therapy often involves a combination of calorie restriction, behaviour modification, increased exercise and pharmacotherapy. Behaviour modification in the treatment regimen may help slow the tendency toward weight regain, but does not prevent it entirely. Unfortunately, the medical treatment of morbid obesity provides minimal sustained weight loss in the majority of patients [25,26]. The fact that morbid obesity remains largely refractory to dietary and medication therapy makes bariatric surgery a viable option [27].

Patients with a BMI of greater than 40 Kg/m^2 ^or 35 to 39.9 Kg/m^2 ^and associated to comorbidities are candidates for bariatric surgery. The most often employed surgical methods are divided into three groups: restrictive, malabsorptive and mixed [28,29]. The most common techniques are Fobi-Capella surgery and Scopinaro's biliopancreatic diversion, which are mixed techniques [30].

This study will sleep study, respiratory mechanics, chemosensitive response and quality of life in morbidly obese patients undergoing bariatric surgery.

### Aims and hypotheses

The aims of this study are to assess the evolution of pulmonary function through spirometry, ventilatory mechanics and breathing tests as well as sleep study parameters and quality of life in subjects suffering from morbid obesity undergoing bariatric surgery and determine a possible correlation between weight loss and these physiological variables. We hypothesise that the weight loss induced by surgical intervention reduces the impact of this disease on sleep quality, cardiovascular consequences and quality of life as well as financial expenditures on treatment.

## Methods/design

### Study design

The study design is a parallel-group randomised controlled trial and is summarised in Figure 1, and is being conducted according to the ethical standards established in the 1961 Declaration of Helsinki (as revised in Hong Kong in 1989 and in Edimburgh, Scotland in 2000). This study is registered with the World Health Organization Universal Trial Number (UTN) U1111-1121-8873, and *Registro Brasileiro de Ensaios Clínicos *(RBR-9k9hhv), and has been approved by the Human Research Ethics Committees of the Nove de Julho University, São Paulo, Brazil (process number 220506/2009). All participants gave written, informed consent.

**Figure 1 F1:**
[figure not shown]
**Flowchart representing the study design**.

### Subjects and recruitment procedure

Individuals with morbid obesity (BMI between 40 kg/m^2 ^and 50 Kg/m^2^) or BMI between 35 kg/m^2 ^and 39.9 kg/m^2 ^associated to comorbidities will be recruited from the surgery ward of the Santa Casa de Misericórdia Hospital of the city of Sao Paulo (Brazil) and sent to the Sleep Laboratory of the *Universidade Nove de Julho*, Sao Paulo (Brazil). Participants will be recruited consecutively and screened for eligibility using a standardised protocol. The eligibility criteria are described below.

### Inclusion Criteria

1- Grade III morbid obesity (BMI ≥ 40 kg/m^2^) or ≥ 35 kg/m^2 ^with comorbidities;

2- Male and female patients aged 18 to 65 years;

3- Documented history of conventional weight loss attempts having proven unsuccessful over time;

4- Agreement to participate in the study through a signed term of informed consent.

### Exclusion Criteria

1- Any medical condition rendering surgery too risky;

2- BMI above 55 kg/m^2^;

3- Clinically significant or unstable mental health concerns;

4- Unrealistic postoperative target weight and/or unrealistic expectations of surgical treatment;

5- Pregnancy, lactation or planned pregnancy within two years of potential surgical treatment;

6- Lack of safe access to abdominal cavity or gastrointestinal tract;

7- Smoking (at least 8 weeks prior to surgery), abusive alcohol use or drug use.

### Randomisation

Following the initial evaluation and fulfilment of the eligibility criteria, the subjects will be randomly distributed into an intervention group [bariatric surgery group (BSG)] and control group (CG). Randomisation numbers will be generated using a randomisation table at a central office. A series of numbered, sealed, opaque envelopes will be used to ensure confidentiality. Each envelope will contain a card stipulating to which group the subject will be allocated. This randomisation criterion will be used due to the enormous number of candidates for bariatric surgery and the limited capacity of the surgical ward to meet this demand. All subjects submitted to this randomisation protocol will meet the eligibility criteria and will be clinically stable.

### Sample size

A previous study published by Lettieri et al. (2008) [31] identified a mean reduction in the Apnoea-Hypnoea Index of 23.4 events/hour in morbidly obese patients submitted to bariatric surgery (expected size effect). Using a standard deviation of 22.8 events/hour from the same study and considering α = 0.05 and power = 80%, the sample was estimated as 17 patients.

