#### Educational and psychological program

During the initial evaluations, all patients will take part in an educational program in the auditorium of Santa Casa de Misericordia Hospital, where they will receive information on the development and progression of obesity, treatment (pharmacological and non-pharmacological) and the importance of regular physical activity practice. All patients will receive a chart containing the educational program [38].

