### Statistical analysis

Data will be presented as means ± standard deviation, when applicable. For comparison of continuous variables before and after bariatric surgery, it will be used the paired Student t-test or Wilcoxon tests as appropriate. Comparisons between groups will be performed using Student *t *test or Mann-Whitney U according to the distribution.

All tests will be 2 tailed, and p values of less than 0.05 will be assumed to represent statistical significance. Multivariate linear regression will be used to identify independent predictors of the AHI following surgical weight loss. All analyses will be done using SPSS ver. 16.0 [55].

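### The planning effect of 23.4 events/h is a fall in operated patients, not a between-group difference net of control change; 80% power for the randomised comparison has almost no margin

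*Protocol article*

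**What the plan says.** - **Planning effect** (Sample size): an earlier study "identified a mean reduction in the Apnoea-Hypnoea Index of 23.4 events/hour in morbidly obese patients submitted to bariatric surgery (expected size effect").
- **Spread** (Sample size): "Using a standard deviation of 22.8 events/hour from the same study". The text does not say whether this is the SD of the change or of AHI at one visit.
- **Result** (Sample size): "considering α = 0.05 and power = 80%, the sample was estimated as 17 patients". It does not say whether that is per group, in total, or in the surgery group alone.
- **Design** (Study design): "The study design is a parallel-group randomised controlled trial". The Randomisation section allocates patients to surgery or control.
- **Tests** (Statistical analysis): "All tests will be 2 tailed". Paired tests are planned for before against after surgery, and Student's t or Mann-Whitney between groups. The sample size is tied to neither.
- **Entry** (Inclusion Criteria, Exclusion Criteria): BMI, age, failed conventional weight loss and fitness for surgery. Neither list requires sleep apnoea or a minimum AHI.

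**The concern.** A randomised comparison estimates the change in operated patients minus the change in controls. A fall measured in operated patients equals that difference only if controls do not change. It carries over to this trial only if these patients start from an AHI similar to that of the cited cohort. The Sample size section states neither condition. The second matters because AHI cannot go below zero: a mean fall of 23.4 needs a mean baseline above 23.4, and the entry criteria do not secure one. If the net difference is somewhat smaller than 23.4, the between-group comparison has less than the advertised 80% power, and a null result would be hard to interpret.

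**Working it through.** **Inputs.** Difference 23.4 events/h, SD 22.8, alpha 0.05 and power 80% from Sample size; two-sided testing from Statistical analysis. Assumed because not stated: 1:1 allocation, no dropout, and 22.8 as the SD of whatever is compared between groups.

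**1. Reproducing 17.**
- Two groups, normal approximation: n per group = 2 × [22.8 × (1.960 + 0.842) / 23.4]² = 14.9, so 15.
- Two groups, t-test: 15.9, so 16 per group.
- The two-group t result divided by 0.955, the usual Mann-Whitney efficiency: 15.92 / 0.955 = 16.7, so 17 per group.
- One group, paired t-test, SD of change 22.8: 9.5, so 10.
- One group, paired t-test, SD of change 22.8 × √2 = 32.2 (22.8 at each visit, zero correlation): 16.9, so 17.
- 17 as the total of two groups does not reproduce: 30 to 32 would be needed.

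So 17 fits a per-group figure for two groups, and also a single-group paired calculation. The arithmetic cannot settle which was meant.

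**2. Power with 17 per group (the favourable reading).** For a two-sample t-test on 32 degrees of freedom, the noncentrality is (D / 22.8) × √(17/2), where D is the net between-group difference. At D = 23.4 this is 1.026 × 2.915 = 2.99, and power is 83%.

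**3. Margin.** Solving for 80% power at 17 per group gives D = 22.6. The slack is 23.4 − 22.6 = 0.8 events/h. With the normal approximation the limit is 21.9 and the slack 1.5.

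**4. Smaller net differences.** The control falls are assumptions; the documents give none.

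| Assumed control fall | Net difference D | Power, 17 per group (t-test) |
|---|---|---|
| 0 | 23.4 | 83% |
| 3 | 20.4 | 72% |
| 5 | 18.4 | 63% |
| 8 | 15.4 | 48% |

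The same powers apply if D is smaller because baseline AHI is lower than in the cited cohort, provided that the SD stays at 22.8.

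**5. If 17 is the total.** With 8 against 9 patients and D = 23.4, the noncentrality is 1.026 × √(8 × 9 / 17) = 2.11 on 15 degrees of freedom, and power is about 51%.

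**The case against.** The strongest reply is that the plan may be adequate as it stands. On its own inputs, 17 per group gives 83% power. The protocol also gives reasons to expect little change in controls: entry requires "Documented history of conventional weight loss attempts having proven unsuccessful over time", and the Background says that medical treatment brings minimal lasting weight loss. The statement that "all patients will take part in an educational program" does not clearly point the other way, since the programme goes to both groups and an additive effect would cancel. This stands, and it is why the point is one of conditional power.

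A reader might infer more than the documents support:
- **That the cited study was uncontrolled.** The protocol calls it only a previous study.
- **That its cohort was enriched for sleep apnoea, so the effect should be scaled down.** The cohort is described as morbidly obese, the same label as this trial's patients. If it was equally unselected, 23.4 already averages over patients with low AHI, and scaling would count the dilution twice. The Background adds that sleep apnoea is 12- to 30-fold more frequent in grade III obesity than in the general population.
- **That controls will fall by regression to the mean.** That needs selection on high AHI, and there is none.
- **That 23.4 was certainly used as a between-group difference.** A paired calculation also gives 17. If that was the basis, the control-change argument does not apply to the calculation, but the randomised comparison was then never sized.

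What survives the reply is that the section leaves the target comparison open and leaves almost no room for a smaller net effect.

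**Conclusion.** The concern holds in a limited form. The stated 80% applies to the randomised comparison only if 17 is per group, controls improve by less than about 1 event/h, baseline AHI resembles that of the cited cohort, and 22.8 is the right SD. None of these is stated. Under modest assumed departures, power runs from 72% down to 48%; if 17 is the total, it is about 51% with no departure at all. It would be tempting to say flatly that the power is overstated. The documents do not support that, because nothing in them shows a true net difference below 22.6.

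**What to change.** **Sample size section.** State that the planning difference is the between-group difference in AHI net of control change, and justify 23.4, or another value, on that basis. State that 17 is per group; if it was meant as the total or as a paired calculation, redo it for the between-group comparison. Say what the 22.8 is the SD of. Give power over a range of smaller net differences, as in the table above.

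**Statistical analysis section.** Compare groups on follow-up AHI with a model that includes baseline AHI (ANCOVA), in place of the unadjusted t or Mann-Whitney test for this outcome. Baseline AHI already comes from the pre-surgical polysomnography, and to the extent that it predicts follow-up AHI the adjustment improves precision. The model needs follow-up polysomnography in controls as well, so the text should say so explicitly.

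A minimum AHI at entry is not needed. Although the Randomisation section mentions "the enormous number of candidates for bariatric surgery", such a criterion would change the population for the lung-function and quality-of-life aims too.

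**Cost.** Protocol wording, a less favourable stated power and slightly more analysis work. No new measurement is needed if controls already have follow-up polysomnography.

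### The sample of 17 patients is not labelled per group, surgery group or total; as the total for this two-arm trial it gives about 51% power, not 80%

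*Protocol article*

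**What the plan says.** The Sample size section takes its effect from a published study of operated patients: a "mean reduction in the Apnoea-Hypnoea Index of 23.4 events/hour in morbidly obese patients submitted to bariatric surgery (expected size effect"). It continues "Using a standard deviation of 22.8 events/hour from the same study" and concludes "considering α = 0.05 and power = 80%, the sample was estimated as 17 patients". It does not say whether 22.8 describes the AHI level or its change, which test was used, or whether 17 counts one group or both.

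Other sections fix the design. Under Study design: "The study design is a parallel-group randomised controlled trial". Under Randomisation: "the subjects will be randomly distributed into an intervention group [bariatric surgery group (BSG)] and control group (CG"). No allocation ratio is given. Under Statistical analysis, before-after comparisons use a paired t or Wilcoxon test. For the arms, "Comparisons between groups will be performed using Student" t or Mann-Whitney tests, depending on the distribution. The same section adds: "All tests will be 2 tailed, and p values of less than 0.05 will be assumed to represent statistical significance".

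**The concern.** Taken at face value, the sample of a two-arm trial is everyone randomised, so 17 people would be divided between surgery and control. An effect of about one standard deviation cannot be detected with 80% power by a two-sided t test on 8 and 9 patients. Recruitment to 17 and recruitment to 34 are different trials, and the text does not tell the reader which is planned.

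With 17 in total, the randomised comparison would have roughly an even chance of missing the very effect it expects. A null result would say little, and interpretation would tend to fall back on the before-after change in operated patients, which does not use the randomised control group.

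**Working it through.** **Inputs.** Difference 23.4 events/hour, SD 22.8, α = 0.05 and power 80% (Sample size); two-sided testing and Student t between groups (Statistical analysis); two parallel groups (Study design, Randomisation). Assumption: 1:1 allocation, so 17 in total means 8 v 9, the most favourable split. Standardised difference d = 23.4/22.8 = 1.026.

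**Step 1: can 17 be reproduced for the between-group test?** The normal approximation per group is

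n = 2 × [SD × (z₀.₉₇₅ + z₀.₈₀)/difference]² = 2 × [22.8 × (1.960 + 0.842)/23.4]² = 14.9, so 15 per group.

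The exact calculation uses the noncentral t distribution with n₁ + n₂ − 2 degrees of freedom and noncentrality d/√(1/n₁ + 1/n₂):

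| Groups | Total | Noncentrality | Critical t | Power |
|---|---|---|---|---|
| 15 v 15 | 30 | 2.811 | 2.048 | 77.4% |
| 16 v 16 | 32 | 2.903 | 2.042 | 80.2% |
| 17 v 17 | 34 | 2.992 | 2.037 | 82.7% |

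The t test therefore needs 16 per group. A figure of 17 per group is close to this, one above the minimum, but is not an exact match.

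**Step 2: 17 as the total.** For 8 v 9 the noncentrality is 1.026/√(1/8 + 1/9) = 2.112, against a critical t of 2.131 on 15 degrees of freedom. Power is 50.7%. The normal approximation gives Φ(2.112 − 1.960) = Φ(0.152) = 56.0%. A one-sided t test, which the plan does not use, would give 64.5%. The difference detectable with 80% power at 8 v 9 (two-sided t) is 33.2 events/hour, against the 23.4 assumed.

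**Step 3: 17 from a paired before-after test.** The result depends on what 22.8 is.

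- *SD of the change:* noncentrality is 1.026 × √n. With n = 9 power is 76.9%, with n = 10 it is 82.3%, so 10 patients suffice. With n = 17 power is 97.8%.
- *SD of the level, with zero correlation between the two measurements:* the SD of the change is 22.8 × √2 = 32.24, and 23.4/32.24 = 0.726. With n = 16 power is 77.4%, with n = 17 it is 80.2%, so exactly 17 are needed.
- *SD of the level, with positive correlation:* fewer are needed, for example 14 at a correlation of 0.2 and 10 at 0.5.

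In each paired case the count is of operated patients only. It says nothing about the control group.

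**Summary of readings**

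| Reading of 17 | Reproduces the stated 80%? | Power of the randomised comparison |
|---|---|---|
| Total, two-sample t | No | 50.7% |
| Per group, two-sample t | Nearly (16 needed) | 82.7% |
| Operated patients, paired, SD of level, zero correlation | Yes (80.2%) | Not given; depends on the control group size |
| Operated patients, paired, SD of change | No (10 needed) | Not given; depends on the control group size |

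**The case against.** The article never says that 17 is the total. If 17 per group is meant, the trial slightly exceeds its stated power and only a label is missing. The 51% also rests on 1:1 allocation, which is not stated. All of this is right, and it means that an arithmetic error has not been proven.

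A reader might go further and infer that 17 can only mean 17 per group, since the between-group test needs 16 and the paired test 10. The document does not support that. The paired figure of 10 assumes that 22.8 is the SD of the change, which the text does not say. If it is the SD of the level and the correlation is taken as zero, a paired test needs exactly 17 operated patients. This reading has some support in the text: the effect is a reduction in operated patients, the paired test is listed first, and the repeat visits at 30, 90 and 360 days are described for operated patients. It does not rescue 17 as a two-arm total, because it counts one arm only.

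A reader might also fault the paragraph for making no allowance for loss to follow-up over 360 days. That is not pressed here. A condensed article commonly leaves such detail to the full protocol, and any power figure after loss would rest on a loss rate that the document does not give.

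**Conclusion.** The concern holds in this form: the sample size sentence does not identify what 17 counts, and on its literal reading the stated power is not delivered. As the total, 17 gives about 51% power (56% by the normal approximation) for the planned two-sided comparison, with a detectable difference of about 33 events/hour. This assumes the plan's own 23.4 and 22.8, with 22.8 serving as the SD of the outcome compared between groups, and an 8 v 9 split; a more unequal split lowers the power further. The randomised comparison needs 32 patients in total, and 34 would give about 83%. It remains open whether 17 came from a between-group or a paired calculation; the text does not settle it. Neither origin supports 17 as the total for the randomised comparison at 80% power.

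**What to change.** Restate the Sample size paragraph for the randomised between-group comparison. Name the test, say whether 22.8 is the SD of the AHI level or of its change, and give the number per group and in total. The rest depends on what was planned:

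- If 17 per group, state 34 in total and power of about 83%.
- If 17 in total, keep the number and restate the power as about 51%, with a detectable difference of about 33 events/hour.
- If 17 is the surgery group from a paired calculation, say so, and add the between-group power for the actual group sizes.

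The authors should report the calculation that was actually done; the wording should not present a two-sample calculation as the original basis unless it was. The cost is a few sentences and no change to procedures. The drawback is that the stated power may become less favourable.
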